## Abstract

**Background:**

Healthy lifestyles are crucial for preventing chronic diseases. Nonetheless, approximately 90% of Chinese community residents regularly engage in at least one unhealthy lifestyle. Mobile smart devices-based health interventions (mHealth) that incorporate theoretical frameworks regarding behavioral change in interaction with the environment may provide an appealing and cost-effective approach for promoting sustainable adaptations of healthier lifestyles. We designed a randomized controlled trial (RCT) to evaluate the effectiveness of a socioecological model-guided, smart device-based, and self-management-oriented lifestyles (3SLIFE) intervention, to promote healthy lifestyles among Chinese community residents.

**Methods:**

This two-arm, parallel, cluster-RCT with a 6-month intervention and 6-month follow-up period foresees to randomize a total of 20 communities/villages from 4 townships in a 1:1 ratio to either intervention or control. Within these communities, a total of at least 256 community residents will be enrolled. The experimental group will receive a multi-level intervention based on the socioecological model supplemented with a multi-dimensional empowerment approach. The control group will receive information only. The primary outcome is the reduction of modifiable unhealthy lifestyles at six months, including smoking, excess alcohol consumption, physical inactivity, unbalanced diet, and overweight/obesity. A reduction by one unhealthy behavior measured with the Healthy Lifestyle Index Score (HLIS) will be considered favorable. Secondary outcomes include reduction of specific unhealthy lifestyles at 3 months, 9 months, and 12 months, and mental health outcomes such as depression measured with PHQ-9, social outcomes such as social support measured with the modified Multidimensional Scale of Perceived Social Support, clinical outcomes such as obesity, and biomedical outcomes such as the development of gut microbiota. Data will be analyzed with mixed effects generalized linear models with family and link function determined by outcome distribution and accounting for clustering of participants in communities.

**Discussion:**

This study will provide evidence concerning the effect of a mHealth intervention that incorporates a behavioral change theoretical framework on cultivating and maintaining healthy lifestyles in community residents. The study will provide insights into research on and application of similar mHealth intervention strategies to promote healthy lifestyles in community populations and settings.

**Trial registration number:**

ChiCTR2300070575. Date of registration: April 17, 2023. https://www.chictr.org.cn/index.aspx.

## Introduction

Healthy Lifestyles, including regular physical activity (PA), balanced diet, smoking cessation, limited alcohol consumption, and healthy body weight, are important contributors to preventing and controlling chronic diseases [1]. In contrast, unhealthy lifestyles are associated with increased risks of cardiovascular and metabolic diseases, as well as mortality [2, 3]. Unfortunately, about 89.6% of Chinese community-resident adults engage in at least one unhealthy lifestyle [2]. Accordingly, there is a need for effective intervention strategies targeting modifiable unhealthy lifestyles.

Traditional community-based intervention studies have typically been implemented at specific geophysical sites [4, 5]. While evidence suggests that such interventions can be effective in promoting and maintaining favorable lifestyles, they can be resource-intensive and costly [6]. Moreover, participants often discontinue participation if they find the interventions unappealing or time-consuming [7, 8]. In comparison, facilitated by the widespread adaptation of smartphones, mobile smart device-based health interventions (mHealth) appear easier to implement on a larger scale and more cost-effective [6, 9]. mHealth interventions can incorporate multidimensional lifestyles management strategies [10], utilizing a range of tools, including text messages, remote health monitoring [10, 11], and web-based programs with digital resources (e.g., videos) [12]. Through timely feedback from participants the strategy itself can furthermore be continuously adapted. Previous randomized controlled trials (RCTs) evaluating mHealth interventions in community dwelling adults have mainly focused on one or two specific lifestyle behaviors (e.g., PA and diet). Behavioral modifications achieved were negligible [13–15], or not sustained [16], in about half of the studies, with the other half demonstrating mostly short term effects [17–19]. One possible reason may be that mHealth interventions for healthy lifestyles are influenced by multi-level environmental factors, including individual, community and policy-level determinants [20–23]. Currently, only a few of community-based RCTs implemented mHealth intervention at multi-level [24, 25]. For example, Tamura and colleges developed a multilevel (individual, work, home, church levels) mHealth PA intervention in resource-limited communities [24]; Hosteng et al., evaluated a mHealth PA intervention that considered individual and social levels [25]. These studies indicated the effectiveness of multilevel mHealth intervention while fail to consider participants’ self-management.

The socioecological model provides a useful theoretical framework that can help to understand how society, community, and individual level factors affect lifestyles and health outcomes of community residents [26, 27]. However, the social-ecological model has also been criticized for lacking an agency dimension that considers people’s decision making and self-management strategies [27, 28]. Empowerment models, in turn, focus on the agency dimension and people’s self-management strategies, emphasizing opportunities to develop self-management skills, social engagement and personalization of goals [29], but neglect the multilayered nature of environmental influences [11]. An integration of empowerment and socio-ecological models may thus be a promising framework to guide smart device-based, and self-management-oriented lifestyle interventions for community residents [30].

The development of mHealth interventions that are guided by the socioecological model and supported by multi-dimension empowerment theory is likely to better promote the adaptation and maintenance of an array of healthy lifestyles, leading to systematic and lifelong health benefits. Therefore, we designed a randomized-controlled community-based trial, named 3SLIFE (i.e., socioecological model-guided, smart device-based, and self-management-oriented lifestyles). The 3SLIFE trial aims to evaluate a mHealth-based intervention that is theoretically supported by empowerment theory and socio-ecological model to promote healthy lifestyles among community residents in China.

## Methods

The protocol has been developed according to the Standard Protocol Items: Recommendations for Interventional Trials (SPIRIT) statement [31] and interventions are described according to the Template for the Intervention Description and Replication (TIDieR) framework [32].

### Study design overview

This is a two-arm, parallel, cluster-RCT targeting the promotion of healthy lifestyle among community residents in China. The study design and intended participant flow through the study is shown in Fig. 1. The study includes a 6-month intervention and a 6-month follow-up phase. We hypothesize that participants in the intervention group will more frequently change unhealthy behaviors towards healthy lifestyle patterns than those in the control group.

**Fig. 1 Fig1:**
[figure not shown]
Study design and anticipated participant flow

### Settings and participants

The study will be embedded in the China Multi-Ethnic Cohort (CMEC) [33], which uses a multistage random sampling strategy to select participants. Four towns (administrative areas in China with about 300,000 inhabitants) will be randomly selected from 18 towns that have undergone two survey waves within the CMEC, and used as the study sites. A total of 20 eligible communities/villages will further be randomly selected within the four towns. These will then be randomized to control or intervention. Eventually, community-dwelling adults from these communities/villages will be screened for eligibility and those who meet the eligible criteria will be invited to participate.

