##### Recruitment method

The community/village is confirmed by the governmental committee of the town (after having been randomly selected), then preliminary screening of candidate participants will be conducted.

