### Randomization and allocation concealment

In this cluster-RCT, recruitment and baseline data collection will be conducted prior to randomization. Cluster randomization, which is necessary for implementation of community-level interventions, mitigates concerns of within-community/village contamination, and improves the feasibility of on-site intervention, will be performed at the community/village level. A total of 20 eligible communities/villages will be randomized using a computer-based random number generator (www.random.org) and assigned to either the intervention group or the control group, with 10 communities/villages in each group. A covariate adaptive procedure will be used to minimize the *P* value from a joint *F* test (1000 iterations) to facilitate covariate balance [34, 35]. Several location level covariates will be considered, including number of village residents, and mean age and sex ratio of residents.

Allocation concealment will be ensured through central randomization [36]. Specifically, an independent statistician will generate a block randomization sequence with randomly permutated block size (4–8) and 1:1 allocation ratio. A sequential list with resulting random numbers will be provided to the study center that recruits villages. Only after participation of a village is confirmed, will the study center reveal labels of the random sequence to the trial team delivering interventions.

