### Timeline of data collection

Participants who meet the inclusion criteria will undergo baseline data collection given informed consent. Communities will only be randomized after this baseline data collection, with corresponding allocation of participants to experimental or control group. Demographic characteristics and medical records data will respectively be surveyed and extracted at baseline. Primary outcome and secondary outcomes assessed with questionnaires and scales will be collected at five measurement points: baseline, 3 months after baseline, primary end-point. That is end of instructed intervention period (6-month follow-up), 9-month follow-up, and 12-month follow-up. Laboratory data will be collected at four time points: baseline, 3 months, primary end-point (6-month), and 12-month follow-up (Fig. 3).

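### The protocol gives two opposite orders for randomising villages and enrolling residents, and two allocation mechanisms without saying which sets a village's arm

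*Protocol article*

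**What the plan says.** All references are to the Protocol article.

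**Order.** *Settings and participants* describes the selection of 20 villages and continues: "These will then be randomized to control or intervention. Eventually, community-dwelling adults from these communities/villages will be screened for eligibility". *Randomization and allocation concealment*, first paragraph, says that "recruitment and baseline data collection will be conducted prior to randomization". *Timeline of data collection* agrees with the latter: "Communities will only be randomized after this baseline data collection".

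**Release of labels.** The second paragraph of the randomisation section says: "Only after participation of a village is confirmed, will the study center reveal labels of the random sequence to the trial team delivering interventions". Under *Recruitment method* for study sites, the town's committee confirms the village and "then preliminary screening of candidate participants will be conducted".

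**Mechanism.** The first paragraph of the randomisation section assigns 20 villages, 10 per arm, with a random number generator. It adds a covariate-adaptive step of 1000 iterations that minimises the P value of a joint F test on village covariates. The second paragraph says that "an independent statistician will generate a block randomization sequence with randomly permutated block size" of 4–8 at a 1:1 ratio, and that the resulting sequential list goes to the study centre that recruits villages.

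**The concern.** In a cluster trial, concealing the sequence at village level does not protect the enrolment of individuals. If residents are identified and invited once the arm is known, those who agree can differ between arms, for example in readiness to change. Intention-to-treat preserves the groups as enrolled, so it preserves that difference too. The primary outcome depends on motivation, since it is a fall of at least one unhealthy lifestyle, mostly self-reported. The expected control rate is only 2%, so a small shift in who is enrolled matters.

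The second problem is that a reader cannot tell how a village gets its arm. A balance-driven choice among allocations of all 20 villages needs every village and its covariates in hand. A sequential list revealed as villages are confirmed does not. The article does not say how the two combine.

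**Working it through.** **1. The order, side by side.**

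| Section | Sequence |
|---|---|
| *Settings and participants* | select villages → randomise → screen and invite residents |
| *Randomization*, paragraph 1 | recruit, baseline → randomise |
| *Timeline of data collection* | consent, baseline → randomise |
| *Randomization*, paragraph 2 | village confirmed → labels may be released; residents' enrolment not mentioned |
| *Recruitment method* (sites) | village confirmed → preliminary screening of residents |

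Row 1 contradicts rows 2 and 3 outright. Rows 4 and 5 together would permit release before residents are enrolled, but only if both mean the same confirmation. The site exclusion criterion (fewer than 5 eligible residents) also implies some screening before randomisation. Under row 1, a village could be found ineligible after it had been allocated.

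**2. The plan's sample size, used as a scale.** Inputs from *Sample size*: 2% versus 12%, alpha 0.05, power 0.80. With pooled variance under the null, two-sided:

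n = [1.960·√(2·0.07·0.93) + 0.842·√(0.02·0.98 + 0.12·0.88)]² / 0.10² = [0.707 + 0.298]² / 0.01 ≈ 101.0, rounded up to 102 per arm.

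102/0.8 = 127.5, so 128. Both figures agree with the protocol. Expected favourable outcomes are 0.02·102 ≈ 2 and 0.12·102 ≈ 12, a difference of about ten people per arm.

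**3. What selection could do (illustration).** Assume no true effect, a 2% control rate, and an intervention-arm rate raised to x by post-allocation recruitment alone, with 102 per arm and clustering ignored. The chance of a significant result favouring intervention is

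Φ{[(x − 0.02)·√102 − 1.960·√(2·p̄·(1 − p̄))] / √(0.02·0.98 + x·(1 − x))}, where p̄ = (0.02 + x)/2.

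| x | Chance |
|---|---|
| 2% (no selection) | 2.5% |
| 3% | 6.6% |
| 4% | 13% |
| 5% | 21% |

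For x = 4%: (0.2020 − 0.4728)/0.2408 = −1.125, and Φ = 0.130. The values of x are assumed; the article gives no basis for them.

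**4. Does a block list give 10:10?** Let f(r) be the probability of balance over the last r places, with blocks drawn at random from the allowed sizes and the last block cut at village 20. A block of size b ≤ r contributes f(r − b). A cut block contributes C(b/2, r/2)²/C(b, r).

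- Sizes 4, 6, 8, equally likely: f(2) = 0.613, f(4) = 0.705, f(6) = 0.728, f(8) = 0.772, f(10) = 0.682, f(12) = 0.735, f(14) = 0.727, f(16) = 0.730. Hence f(20) = (0.730 + 0.727 + 0.735)/3 = **0.73**.
- Sizes 4 and 8, equally likely: f(4) = (1 + 36/70)/2 = 0.757, f(8) = 0.879, f(12) = 0.818, f(16) = 0.848. Hence f(20) = (0.848 + 0.818)/2 = **0.83**.

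The misses are almost all 9:11.

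**5. Direction of the balance criterion.** A joint F test of village covariates on arm gives a small P value when the arms differ and a large one when they are alike. Keeping the allocation with the smallest P value of 1000 therefore keeps the least balanced one.

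**The case against.** The strongest reply is that the order is fixed where it matters. The two operative sections agree, and the conflicting sentence stands in a setting description that already speaks of eligible villages. Other features also limit differential recruitment. Candidates must have taken part in two earlier cohort survey waves, and some exclusions come from insurance records. Participants and assessors are to be blinded, and controls receive a parallel placebo programme. This stands as far as it goes: following the later sections largely removes the recruitment risk. It does not make the conflicting sentence harmless, because it states a sequence and staff could follow it.

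A reader might infer more in four places, and the documents do not support it:

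- *That the release rule certainly discloses arms before screening.* The article does not define when participation counts as confirmed. Its wording sets a necessary condition, not a moment of release, and labels go to the team delivering interventions. The reading is possible because Table 1 lists local medical workers as providers and *Quality control and quality assurance* has local health professionals helping to schedule participants. It remains an inference.
- *That the two mechanisms cannot coexist.* Blocked sequences could be generated repeatedly and one kept on a balance criterion. The text neither describes nor excludes this.
- *That the 10:10 split will be missed in about a quarter of cases.* This depends on the assumed sizes and on cutting the list blindly. A statistician who knows there are 20 villages can choose blocks that sum to 20, such as 4 + 8 + 8, and a 9:11 split would matter little.
- *That inviting a handful of motivated residents would mimic the target effect.* The 10-point difference needs about ten extra responders per 102. Step 3 shows inflated false positives, not a bias as large as the effect.

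**Conclusion.** The point holds as a contradiction in the text. One section randomises before residents are screened and two sections do the reverse. The label-release rule is not tied to completed enrolment or baseline. Two allocation mechanisms are described with no statement of which determines the arm, and the balance criterion runs in the wrong direction if taken literally.

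The bias is conditional on the first order being followed, and the documents do not show that it will be. Under the assumed shifts in step 3, false positives favouring intervention would rise from 2.5% to between 6.6% and 21%. The block list by itself gives 10:10 with probability 0.73 to 0.83 under the assumptions in step 4. This supports only the claim that it does not guarantee the stated split. Figures 1 and 3 were not available and may bear on the order. The matter should be settled before recruitment, because the order of enrolment and allocation cannot be repaired in the analysis.

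**What to change.** 1. Bring *Settings and participants*, *Recruitment method*, *Randomization and allocation concealment* and *Timeline of data collection* to one order: select villages; screen, consent and complete baseline in all 20; lock the list of enrolled residents; allocate; then release labels.
2. Make release of labels conditional on completed enrolment and baseline, not only on a village's confirmed participation.
3. State one allocation mechanism. With all 20 villages available at once, a single balance-constrained 10:10 allocation by the independent statistician fits. If blocks are kept, say how they combine with the balance step and how 10:10 is assured.
4. Correct the balance criterion so that it favours balance: maximise the joint F-test P value, or require a stated minimum.

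The cost is protocol wording, and the intervention cannot start until the last village has finished baseline. The sample size is unchanged.

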### Eligibility criteria of study sites (community/village) and participants

#### Study sites

##### Inclusion criteria

Study sites have undergone two survey waves of the CMEC.The government of the community/village committee conforms to and agrees with this study protocol;No other intervention programs are being implemented in this community/village;Distance of at least 2 km to other included villages to minimize contamination risk.

##### Exclusion criteria

Less than 5 residents of the community in question meet the participant eligibility criteria.

##### Recruitment method

The community/village is confirmed by the governmental committee of the town (after having been randomly selected), then preliminary screening of candidate participants will be conducted.

#### Participants

##### Inclusion criteria

Being 18 years old or above;Having participated in two survey waves of the CMEC;Having access to the internet via a smartphone.

##### Exclusion criteria

Having a history of major psychiatric illnesses (e.g., schizophrenia and bipolar disorder), Parkinson’s disease, severe cognitive or hearing impairment according to medical records obtained from Sichuan Medical Insurance Bureau.Having had major surgery in the past year;Receiving cancer treatment;Pregnant.

##### Termination criteria

Withdrawing informed consent and/or withdrawing from the trial;Development of new serious diseases that makes it inappropriate to continue the interventions as specified in the trial protocol;Experiencing serious adverse events during the intervention phase.

### Randomization and allocation concealment

In this cluster-RCT, recruitment and baseline data collection will be conducted prior to randomization. Cluster randomization, which is necessary for implementation of community-level interventions, mitigates concerns of within-community/village contamination, and improves the feasibility of on-site intervention, will be performed at the community/village level. A total of 20 eligible communities/villages will be randomized using a computer-based random number generator (www.random.org) and assigned to either the intervention group or the control group, with 10 communities/villages in each group. A covariate adaptive procedure will be used to minimize the *P* value from a joint *F* test (1000 iterations) to facilitate covariate balance [34, 35]. Several location level covariates will be considered, including number of village residents, and mean age and sex ratio of residents.

Allocation concealment will be ensured through central randomization [36]. Specifically, an independent statistician will generate a block randomization sequence with randomly permutated block size (4–8) and 1:1 allocation ratio. A sequential list with resulting random numbers will be provided to the study center that recruits villages. Only after participation of a village is confirmed, will the study center reveal labels of the random sequence to the trial team delivering interventions.

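### The allocation rule minimises the joint F-test P value, which selects the least balanced of the 1000 allocations instead of the best balanced

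*Protocol article*

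**What the plan says.** The section Randomization and allocation concealment assigns 20 communities or villages to two arms, "with 10 communities/villages in each group". It then gives the balancing rule: "A covariate adaptive procedure will be used to minimize the *P* value from a joint *F* test (1000 iterations) to facilitate covariate balance". The next sentence names the covariates: "Several location level covariates will be considered, including number of village residents, and mean age and sex ratio of residents".

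The following paragraph of that section describes a permuted-block sequence with block sizes between 4 and 8, issued as a list. It does not mention the F test. No other part of the article says that the P value is maximised or that the F statistic is minimised.

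**The concern.** A joint F test of the covariates against arm measures how well the covariates, taken together, separate the two arms. A low P value is evidence of imbalance. Searching for the lowest P value therefore searches for imbalance, while the sentence gives its purpose as "to facilitate covariate balance".

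If the rule were programmed literally, arm would be confounded by design with the number of residents, mean age and sex ratio. The primary model (Data analysis) contains intervention group, random intercepts for subject nested in village, and a fixed effect for town, but none of these three covariates. Age and gender enter only in a sensitivity analysis, and village size enters nowhere. The imbalance would pass unadjusted into the primary estimate. Allocation of the 20 villages happens once and cannot be repaired afterwards.

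**Working it through.** The article gives no figure for this rule, so there is none to reproduce. The check has two parts: direction and size.

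**Direction.** Regress the arm indicator on p village covariates across K villages. The joint test is

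F = (R²/p) / ((1 − R²)/(K − p − 1)).

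- Identical covariate means in the two arms: R² = 0, so F = 0 and P = 1.
- Arms fully separated by the covariates: R² approaches 1, F grows without limit and P approaches 0.

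P falls steadily as imbalance rises, so the smallest P marks the most imbalanced candidate. This needs no assumption about the covariates.

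**Size: inputs.**

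| Input | Value | Source |
|---|---|---|
| Villages | 20, split 10:10 | Randomization and allocation concealment |
| Candidate allocations | 1000 | same section, "1000 iterations", read as 1000 complete allocations |
| Covariates | 3 | the three named in the same section |
| Covariate distribution | independent standard normal | assumption |

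The degrees of freedom are 3 and 20 − 3 − 1 = 16.

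**Size: results.** Over 500 simulated sets of villages, three choices were compared. Differences are absolute differences between arm means, in units of the standard deviation across the 20 villages.

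| Allocation chosen | Median P | Mean difference per covariate | Mean difference, worst covariate |
|---|---|---|---|
| Smallest P (as written) | 0.0007 | 0.79 | 1.29 |
| One unrestricted random allocation | – | 0.36 | 0.59 |
| Largest P (as intended) | 0.999 | 0.03 | 0.05 |

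The written rule gives 0.79/0.36 = 2.2 times the imbalance of unrestricted randomisation. Repeat runs with 200 and 300 sets gave 0.78 per covariate under the written rule, with 1.29 to 1.30 for the worst covariate.

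**What adjustment would cost.** P = 0.00066 on 3 and 16 degrees of freedom corresponds to F = 9.8. Then

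- R² = 3F/(3F + 16) = 29.4/45.4 = 0.648
- variance inflation = 1/(1 − 0.648) = 2.84
- equivalent number of villages = 20/2.84 ≈ 7

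This applies to a village-level comparison adjusted for all three covariates, which is not the planned primary model. It shows that adding them later would be an expensive remedy.

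**The case against.** The strongest reply is that this is a slip of wording. The intent stands in the same sentence, and an implementer who aimed for balance would probably have programmed the right direction. The two sources cited for the method were not available to check. That reply limits how likely the harm is. It does not make the sentence correct, and the article offers nothing that shows what was programmed.

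Three further points deserve weight.

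- **The magnitudes are illustrative.** They rest on three independent normal covariates, although the article says there are several and names three as examples, and on reading the iterations as complete candidate allocations. This stands for the sizes, not for the direction.
- **The inflation of 2.84 does not describe the planned analysis.** This also stands. Under the planned model the consequence is bias from unadjusted imbalance. Its size depends on how strongly the village covariates predict the outcome, which the article does not give.
- **The permuted-block paragraph describes a different procedure.** If the block list alone assigns the villages, the P-value rule may not determine allocation, and the harm would not follow. The article does not say how the two combine. That is a reason to clarify the section; it does not rescue the rule.

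**Conclusion.** The concern holds. The allocation rule is stated in the wrong direction and contradicts its own purpose, and this follows from the definition of the F test alone. Under the stated simulation assumptions, literal use would give about 0.79 standard deviations of imbalance per covariate, compared with 0.36 if allocation were not constrained at all and 0.03 under the intended rule. Whether the trial was harmed depends on how the rule was programmed and on whether it, or the block list, assigned the villages. Correction is still required: the error is cheap to remove, and its consequence, if it was carried into the program, could not be reversed after allocation.

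**What to change.** 1. In Randomization and allocation concealment, state that the allocation with the largest joint-F P value (equivalently the smallest F statistic) among the 1000 candidates is chosen.
2. Check the direction in the allocation program before it is run. If allocation has already taken place, confirm from the executed program and the achieved balance on village size, mean age and sex ratio which rule was used, and report it.
3. State how the F-test search and the permuted-block list fit together, or remove the one that is not used.

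Optionally, draw one allocation at random from a prespecified best-balanced set, for example the top 10%, instead of taking the single best. This would support a permutation test over that set. The planned analysis is model-based, so the correction does not depend on it.

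The first step costs one word of text and at most one line of code. The second is a short check, and the third needs a sentence or two. The sample size does not change.
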